##### Documentation of the Therapy Content

The content of the 2-week intensive therapy will be documented using multiple methods (RCT1). First, inertial measurement units, specifically the Xsens Dot (Xsens Technologies BV), will be used to measure and document motor activity (quantity and type of movements) during both on-site camp and at-home HABIT-ILE modalities. Each participant will be equipped with three wearable sensors during the 6.5 hours of daily high-dosage therapy: two placed dorsally on the wrists and one on the front of the right thigh. Activity count (based on a predefined threshold for movement) and asymmetry ratio (comparing right and left upper extremities activity) will be calculated and should make it possible to differentiate between uni- and bimanual tasks [55]. Accelerometer data should also make it possible to evaluate participants’ positions to determine whether they are predominantly sitting or standing during therapy sessions, as well as to quantify the percentage of time spent walking. However, inertial measurement unit–based classification remains approximate, and specific tasks cannot be distinguished with certainty. During the on-site modality, interventionists will complete a structured timesheet detailing each activity in terms of duration and type of motor activity performed throughout the day. For the home modality, therapy content will be partly documented based on the prescribed daily program and data extracted from the REAtouch Lite system (session duration and touch count on the screen). Additionally, at the end of each day, participants will report the duration of therapy they were able to complete.

For the follow-up interventions (RCT2), participants will maintain a weekly log over a 9-week period, briefly describing the type and duration of activities performed each day. Monitoring the completion rates of therapy sessions and comparing the hours of therapy actually performed with those planned will enable us to judge the feasibility of setting up such follow-ups.

### Statistical Analysis

#### Overview

Statistical analysis will be performed after the last measurements at the follow-up assessment using RStudio software (version 2023.12.15+402; Posit). Baseline characteristics will be summarized with means and SDs for normally distributed variables, medians and IQRs for nonnormal variables. Baseline group equivalence will be explored descriptively using independent *t* tests or nonparametric equivalents.

#### RCT 1: HABIT-ILE@home vs HABIT-ILE on-Site Camp (2 Weeks)

Non-inferiority statistics will be used to compare the efficacy of the HABIT-ILE@home modality with the HABIT-ILE on-site camp modality. First, within each intervention arm, changes from baseline (T0) to postintervention (T1) will be evaluated for all outcomes. Depending on data normality, paired samples *t* tests or nonparametric equivalents will be applied. Then, the 95% CI of the difference between groups will be computed by comparing group differences in change scores using independent *t* tests or nonparametric equivalents. Noninferiority will be concluded if the lower bound of this interval is above the prespecified NIM. For all outcomes, NIM will be defined as 50% of the difference between the changes observed with a gold standard (ie, CIMT) and a control group [13].

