### Randomization Process

For RCT1, randomization will be performed using pairwise randomization. Participants will first be paired according to lesion side, time since stroke, age, and modified Rankin Scale (mRS) level. Participants in each pair will then be randomized into one of the two groups using an online external blind electronic randomization system [22], which will provide the assignment only after pairing is completed. This procedure will ensure allocation concealment, as investigators will not be able to predict or influence the upcoming allocation. For RCT2, the same procedure will be repeated within each RCT1 allocation arm, such that participants previously assigned to HABIT-ILE@home or HABIT-ILE on-site will be again matched and randomized in the HABIT-ILE@home follow-up subgroup or the nonspecific follow-up subgroup.

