### Sample Size

For RCT1, assessing the noninferiority of HABIT-ILE@home compared to HABIT-ILE on-site, the sample size was calculated using PASS (version 14.0.15; NCSS) for a noninferiority 2-tailed *t* test of the difference between two means. The primary outcome is the change in the upper extremity subscale of the Fugl-Meyer Assessment (FMA-UE) score from baseline to postintervention (T1-T0), with higher scores indicating better motor abilities. We defined the noninferiority margin (NIM) using a method that ensures both clinical and statistical relevance, rather than only relying on the minimal clinically important difference. We chose the NIM as 50% of the difference between the changes observed with the gold-standard treatment and an interventional control group. This method was chosen to provide a more stringent criterion for noninferiority, ensuring that any treatment deemed non-inferior demonstrates a real benefit for stroke patients. As no previous studies have investigated such changes after a HABIT-ILE intervention, the sample size calculation was based on the mean change observed after a CIMT intervention (+5.6 points at FMA-UE; SD 3.1) [13]. The non-inferiority hypothesis was defined as follows: the HABIT-ILE@home intervention will be considered noninferior if the improvement produced is no more than 2.8 points lower than that obtained with the on-site HABIT-ILE intervention on the FMA-UE. An α level of 0.05 and a 1-β level of 0.8 were used for calculation. Under these assumptions, sample size calculation defined a number of 17 participants per group, resulting in a total of 34 participants.

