#### RCT 2: HABIT-ILE@home vs Nonspecific Follow-Up Interventions (9 Weeks)

Superiority statistical analyses will be used to examine changes during the 9-week follow-up period (T2-T1). Depending on the distribution of the data, the analyses will be conducted using either analysis of covariance (ANCOVA; for normally distributed data) or nonparametric equivalents (eg, rank-based ANCOVA) for nonnormally distributed data. Covariates such as initial T1 scores, mRS, and/or type of initial intervention will be included in the model to adjust comparisons. In case of analyses including all three time points, linear mixed-effects models will be used, with baseline score and group allocation entered as fixed effects.

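### RCT1's noninferiority interval uses neither the matching factors nor baseline FMA; if these predict change, the interval is conservative and power is lost

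*Protocol article*

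**What the plan says.** **Randomisation (Randomization Process).** "Participants will first be paired according to lesion side, time since stroke, age, and modified Rankin Scale (mRS) level". Then: "Participants in each pair will then be randomized into one of the two groups". Baseline FMA is not a matching factor. For the second trial, "For RCT2, the same procedure will be repeated within each RCT1 allocation arm".

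**RCT1 analysis (Statistical Analysis, RCT 1).** The deciding interval is described thus: "the 95% CI of the difference between groups will be computed by comparing group differences in change scores using independent" *t* tests, or nonparametric equivalents. The decision rule is: "Noninferiority will be concluded if the lower bound of this interval is above the prespecified NIM". The only paired tests in that section are the within-arm comparisons of T0 with T1.

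**RCT2 analysis (Statistical Analysis, RCT 2).** This is an ANCOVA or a rank-based version of it: "Covariates such as initial T1 scores, mRS, and/or type of initial intervention will be included in the model to adjust comparisons".

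**Sample Size.** The home programme is noninferior if its gain is "no more than 2.8 points lower than that obtained with the on-site HABIT-ILE intervention on the FMA-UE". The planning figure is a gain of "5.6 points at FMA-UE; SD 3.1", with α 0.05 and power 0.8, giving 17 per group. The calculation is for two independent means.

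**The concern.** Matching on prognostic factors balances them between arms, so their contribution largely cancels from the difference in means. An independent *t* test still counts their variance in its standard error. The interval is then wider than the true sampling variation of the estimate, and true noninferiority is missed more often than necessary. Baseline FMA is a separate source of variance: it is measured in everyone, it is not matched on, and the RCT1 comparison uses it only by subtraction.

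The article gives no reason for adjusting RCT2 and not RCT1. Recruitment is closed, so the analysis model is one of the few remaining ways to gain precision.

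**Working it through.** **Inputs from the article:** margin 2.8, SD of change 3.1, 95% CI rule, 17 per arm as the required number, and 48 recruited (24 per arm if all contribute). **Assumed:** true difference 0; within-pair correlation of change ρ (equivalently, the share of variance carried by the matching factors); correlation *r* between baseline and change. The article gives neither correlation.

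**1. The plan's own figure.** For two independent means, margin 2.8 and SD 3.1, a one-sided α of 0.05 gives n = 16 per arm, close to the stated 17. A one-sided α of 0.025, which is what a 95% CI implies, gives 20 (normal) or 21 (*t*). Under the CI rule, the unadjusted test has 72.4% power at 17 per arm and 86.5% at 24.

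**2. Interval half-widths.**
- Independent: t(0.975, 2n−2) × 3.1 × √(2/n). For n = 17 this is 2.17; for n = 24 it is 1.80.
- Paired: t(0.975, n−1) × 3.1 × √(2(1−ρ)/n). For n = 17 this is 2.25, 2.14 and 2.02 at ρ = 0, 0.1 and 0.2. It becomes the narrower of the two only once ρ exceeds about 0.08 (17 pairs) or 0.05 (24 pairs).
- Baseline ANCOVA alone: t(0.975, 2n−3) × 3.1√(1−r²) × √(2/n). For n = 17 this is 2.17 at r = 0 and 2.07 at r = 0.3.

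**3. Independent *t* test applied to paired data** (100,000 simulated trials per row; paired power by noncentral *t*).

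| Per arm | ρ | One-sided error (nominal 0.025) | Power, independent | Power, paired |
|---|---|---|---|---|
| 17 | 0 | 0.025 | 72.4% | 69.6% |
| 17 | 0.1 | 0.019 | 73.3% | 74.1% |
| 17 | 0.2 | 0.015 | 74.4% | 78.9% |
| 24 | 0 | 0.025 | 86.4% | 85.0% |
| 24 | 0.1 | 0.020 | 87.7% | 88.4% |
| 24 | 0.2 | 0.015 | 89.0% | 91.8% |

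The error never rises above nominal.

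**4. ANCOVA with baseline and four separate matching factors** (5,000 simulated trials per row; about 5 degrees of freedom).

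| Per arm | Matching share | r | Power, *t* test | Power, ANCOVA |
|---|---|---|---|---|
| 17 | 0 | 0 | 72% | 70% |
| 17 | 0.1 | 0.1 | 74.1% | 75.9% |
| 17 | 0.1 | 0.3 | 73% | 79% |
| 17 | 0.2 | 0.3 | 75% | 84% |
| 24 | 0.1 | 0.3 | 88% | 92% |
| 24 | 0.2 | 0.3 | 89% | 94% |

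With a share of 0.2 and r = 0.3, coverage of the *t*-test interval at 17 per arm is 97.2%, against 94.9% for ANCOVA. Separate runs put the largest gain at 9 to 10 points for 17 per arm and 5 to 6 points for 24. With nothing to explain, the loss is 2 to 3 points at 17 and about 1 point at 24. If the four covariates capture only half of the pair variance, the gain at 17 per arm falls to 7.3 points (73.4% to 80.7%) for share 0.2 and r = 0.3, and to 0.7 points (73.7% to 74.4%) for share 0.1 and r = 0.1.

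**The case against.** The strongest reply is that the harm is conditional and runs in the safe direction. It requires the matching factors or baseline FMA to predict *change* in FMA, and the article offers no evidence that they do. With ρ = 0 the independent test beats the paired one. The planned test also agrees with the way the trial was sized. All of this stands. It limits the size of the point but does not remove it: factors are normally matched on because they are thought prognostic, and the downside of adjusting is small.

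A reader might infer several stronger things that the article does not support:

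- **That a noninferiority finding would be unsafe.** It would not; the one-sided error is at or below 2.5%.
- **That the trial must be short of power.** About 72% applies at 17 per arm. The plan recruits 48 and the Results section says that all participants have undergone both interventions. Completer numbers are not given, but at 24 per arm the unadjusted test has about 86%.
- **That baseline imbalance is left wholly in the estimate.** Change scores already subtract baseline. Only the part due to any correlation of baseline with change remains.
- **That the optional RCT2 covariate list causes bias.** RCT2 is randomised within RCT1 arm, so leaving that arm out costs precision only, and a final covariate list is commonly left to the SAP.
- **That a nonparametric method must abandon the scale of the margin.** The article names no method. A Hodges-Lehmann interval is in FMA points and estimates the same shift if the distributions differ only in location.
- **That gains would be larger still.** A 30% share would give 75% against 89% at 17 per arm, but nothing in the article supports a share of that size.

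**Conclusion.** The point holds as one of efficiency. RCT1 is randomised within matched pairs and analysed as though it were not, and baseline FMA is left out although RCT2 allows for its own starting score. If these variables predict change, the 95% CI is conservative and power is lost; if they do not, almost nothing is at stake.

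For shares of 0 to 20% and baseline correlations of 0 to 0.3, ANCOVA changes power by about −2 to +10 points at 17 per arm (*t* test about 72–75%) and by about −1 to +6 points at 24 per arm (*t* test about 86–90%). These figures rest on assumed correlations, a true difference of zero, and the planning SD and margin. Both of the latter are stated for the upper-extremity subscale, whereas the Primary Outcomes section names the total motor score, so the SD of 3.1 may not carry over to the endpoint analysed.

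**What to change.** Make the RCT1 primary analysis an ANCOVA of T1 FMA (or of change) on arm, baseline FMA, lesion side, time since stroke, age and mRS. Compare the 95% CI of the adjusted mean difference with the margin. Use covariates rather than within-pair differences, so that a participant whose partner is lost still contributes; the plan allows for about 30% attrition. Fix the model before allocation is linked to outcome.

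Two minor additions: always include T1 score and RCT1 arm in the RCT2 model, and if residuals are clearly non-normal, use a bootstrap CI for the same mean difference.

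Cost: a change of wording, with no new data, because every covariate is already needed for pairing or as an outcome. The statistical price is about 5 degrees of freedom and, if the covariates explain nothing, up to about 2 to 3 points of power at 17 per arm.

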#### RCT 2: HABIT-ILE@home vs Nonspecific Follow-Up Interventions (9 Weeks)

Superiority statistical analyses will be used to examine changes during the 9-week follow-up period (T2-T1). Depending on the distribution of the data, the analyses will be conducted using either analysis of covariance (ANCOVA; for normally distributed data) or nonparametric equivalents (eg, rank-based ANCOVA) for nonnormally distributed data. Covariates such as initial T1 scores, mRS, and/or type of initial intervention will be included in the model to adjust comparisons. In case of analyses including all three time points, linear mixed-effects models will be used, with baseline score and group allocation entered as fixed effects.

#### Feasibility and Adherence

For questionnaire items shared by both groups, between-group comparisons will use Wilcoxon rank-sum tests. Items specific to the home-based condition will be summarized descriptively.

#### Missing Data

All analyses will follow an intention-to-treat approach. Missing data will be addressed using multiple imputation. All variables and auxiliary variables predictive of missingness will be included in the imputation model.

#### Clinical Significance

The proportion of participants exceeding established minimal clinically important differences on each outcome will be reported for both groups.

## Results

Recruitment started in March 2023 and ended in March 2025. All participants have been recruited and have undergone interventions in RCT1 and RCT2. Data analysis is expected to start in spring 2026.

## Discussion

### Principal Findings

Previous studies have shown that home-based telerehabilitation may be as effective as in-person therapies [56] with good treatment adherence [57]. Specifically, intensive interventions based on motor skill learning principles such as CIMT have shown similar effectiveness at home (both with or without a rehabilitation device) compared to in-person CIMT [19] or standard therapy [58]. Based on these previous results, we anticipate similar improvements when comparing HABIT-ILE@home and HABIT-ILE on-site camp within the first RCT.

However, there may be some challenges for participants to engage in such an intensive home intervention (short duration, high dosage), or even for a home follow-up intervention (longer duration, low to moderate dosage). The higher dosage of the therapy (65 hours) compared to previous studies may be more difficult for participants and caregivers to manage in terms of tiredness and motivation. Nevertheless, intrinsic motivation developed by participants based on the self-determined functional goals and the perceived usefulness of the therapy might help to maintain their treatment compliance. Indeed, a HABIT-ILE@home pilot study conducted in 3 adults with chronic stroke showed that the perspective of improving their motor control capacities, reaching their goals, and gaining autonomy was their main source of motivation, more than the playful nature of the therapy [54]. The daily program sent each day by the supervision team will aim to target the functional goals considered as important by the participant, thus supporting their intrinsic motivation.

In addition to the patients’ and caregivers’ motivation and adherence to treatment, a second aspect of the home-based protocol that needs to be documented is the burden of treatment. Indeed, caring for patients with chronic stroke may impose a significant burden on caregivers and could lead to heightened levels of anxiety and depression [59]. This affected mental health in caregivers can result in slower progress and poorer overall outcomes for the patient [60]. Moreover, the emotional state of caregivers and stroke patients is interconnected. Patients whose caregivers report greater burdens often exhibit higher levels of anxiety themselves, which could also impact patient improvements [59,61].

Introducing a new rehabilitation approach that involves caregivers may initially increase their burden, as they must understand and adapt to new responsibilities associated with the therapeutic process [61,62]. However, over time, as caregivers gain competence in managing their relative’s health condition, they may experience reduced anxiety and greater satisfaction in their caregiving role [63,64]. This shift highlights the potential of involving the caregivers in rehabilitation to not only enhance the stroke patients’ recovery but also improve the mental health of the caregivers. Involving caregivers in rehabilitation can lead to mutual benefits for themselves and stroke patients, ultimately promoting better health outcomes. However, this can only be achieved if caregivers feel sufficiently supported by therapists by receiving adequate clinical supervision [65]. As planned in the present intervention, previous studies have observed a positive effect of a dedicated initial training to reduce the caregivers’ burden and enhance perceived competence in managing therapeutic tasks, resulting in less stress and a greater engagement in rehabilitation [66].

Based on the current recommendations for motor and functional stroke rehabilitation, we hypothesize that the specific HABIT-ILE@home follow-up will result in better retention of changes following 2-week high-dosage therapies, and even better additional improvements than the nonspecific follow-up intervention (RCT 2) [67,68]. The HABIT-ILE follow-up program follows these recommendations by using a patient-centered approach that focuses on setting individualized goals to shape the therapy. It encourages self-initiated movements through goal-oriented training, promoting motor learning through trial and error. The program also incorporates shaping techniques, where activities are adapted to the patient’s current abilities and gradually become more challenging as they progress. This is further supported by intensive practice sessions designed to maximize the number of repetitions. However, adding 5 hours of home therapy per week to the participants’ usual schedule may be a challenge. Multiple determinants may cause nonadherence to a home-based program: psychological factors, lack of social support, time constraints, and complexity of activities proposed [69,70]. To avoid nonadherence to the prescribed exercise regimen during HABIT-ILE@home follow-up, we plan to set up a weekly schedule of exercises tailored to individual goals of each participant along with gamified activities in addition to the 1-hour supervised session each week [71].

The participants’ adherence to the 2-week HABIT-ILE@home intervention and the 9-week HABIT-ILE@home follow-up, as well as the burden and feasibility of these interventions, will be documented through a satisfaction questionnaire. This should help us highlight some of the pros and cons of such interventions. Another concern that will be investigated is the possibility of adhering to the HABIT-ILE therapeutic principles during the whole therapeutic time in the home-based setting. This will be partially inferred from the accelerometers, REAtouch Lite, and logbook data documenting the content of the therapy. Even if we cannot be sure of the correct application of all the HABIT-ILE principles, we assume that caregivers’ and participants’ training before therapy, provision of a daily detailed treatment schedule, and adequate remote supervision will help to address this concern.

This trial is expected to determine whether HABIT-ILE@home can produce improvements comparable to those obtained during the on-site intensive program across motor, activity, and participation-related outcomes, while substantially reducing logistical and accessibility barriers. Demonstrating noninferiority would support the scalability of high-dose bimanual motor-learning interventions in community settings. The follow-up phase will also provide important insights into the role of structured, task-specific home programs in maintaining or enhancing gains achieved during intensive interventions. If the specific HABIT-ILE@home follow-up proves superior to the nonspecific program, this would highlight the importance of targeted postintensive rehabilitation to promote retention and transfer of improvements into daily life.

### Conclusion

This study will provide evidence on the feasibility and efficacy of delivering HABIT-ILE through a home-based telerehabilitation modality for adults with chronic stroke. Demonstrating noninferiority of HABIT-ILE@home compared to on-site therapy would support wider accessibility to intensive rehabilitation while reducing logistical and human resource constraints. Additionally, showing the added benefit of a structured follow-up could emphasize the importance of continuity of care to sustain and enhance motor recovery after intensive interventions.
